|  | 5d | [name]. [name], Clinic for Internal Medicine I, Ulm (Study leader, Protocol Committee)  [name]. [name], Institute of Medical Systems Biology, Ulm (Study leader, Protocol Committee)  Dr. med. [name], Clinic for Internal Medicine I, Ulm (Study coordinator, Protocol Committee)  [name], Comprehensive cancer centere Ulm (trusted third party)  [name], Institute of Medical Systems Biology, Ulm (Statistic and biometry)  M.sc. [name], Institute of Medical System Biology (Protocol Commiteee)  [name], Institute of Medical System Biology (Protocol Commiteee)  M.sc. [name], Institute of Medical System Biology (Protocol Commiteee)  M.sc. [name], Institute of Medical System Biology (Protocol Commiteee)  [name] [name], Institute of Medical System Biology (Protocol Commiteee)  [name] [name], Institute of Medical System Biology (Protocol Commiteee)  [name], Ulm University Clinic (Protocol Commiteee) |
| Introduction |  |  |
| Background and rationale | 6a | Due to the respective tumor therapy protocols, but also due to limited resources, doctors only see their outpatients at certain intervals. Patients often forget important information about side effects, intolerances and general well-being or do not consider this information relevant.  In particular, drug combination therapies in oncology often contain active ingredients that can cause side effects such as nausea, inflammation of the mucous membrane (mucositis), diarrhea (diarrhea) or polyneuropathy. The acceptance of tumor therapy is decisively determined by the occurrence and duration of the side effects. If the therapy is well tolerated by the reduction of side effects, an improvement in quality of life is achieved. This is an important goal of a tumor therapy that also takes into account the psycho-oncological and social needs of the patients.  For the standardized documentation of possible relevant side effects and other therapy-associated information, an app has been developed to make it easier for patients to record these side effects.  In a first part, the acceptance and applicability of the app will be tested within the scope of the present study. If this first part is completed with positive results, a second phase is planned to investigate the effect of using the app on the management of side effects and their supportive therapy, as well as the maintenance of the original chemotherapy dose. |

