| Trial design | 8 | This study will be implemented in two parts. The first part should evaluate the feasibility and acceptance of a smartphone-based adverse reaction documentation. It will be followed by a second part. which will compare the impact of smartphone reported adverse events regarding applied therapy doses to those of patient with standard care. For the detection of occurred adverse events at an early stage, the participants will answer a standardized questionnaire (Table 1 and 2) via the NEMO app every day. Depending on the underlying therapy scheme, the NEMO questionnaire can be selected for chemotherapy (Table 1) or combined immunotherapy (Table 2), targeted therapy, and chemotherapy. NEMO allows for switching the therapeutic settings in case the therapeutic scheme changes. During therapy sessions, the documented data is transmitted securely via QR-codes to the treating physician and used for future therapy settings. To assess the. feasibility, 30 patients will be divided non-randomly into three age groups (< 55 years, 55-75 years, >75 years) of 10 patients each. These people will be followed over six months. Participants will answer the respective NEMO questionnaire about adverse events on a daily basis over these six months. After six months, they will answer a questionnaire about user-friendliness and feasibility (Table 3). Evaluation of these questionnaires allows for studying the different patients' characters and their potential benefit of using NEMO. The answered questionnaires could also give insights to identify barriers to answering the questions. The results of this evaluation enable us to amend the criteria for recruiting patients of the second part, such as their age and improving the application for the second part of the study. To assess the reduction of adverse events, 36 participants will be randomly assigned a group of 18 persons (smartphone user and standard care). Again, smartphone users will answer their respective NEMO questionnaires every day about occurred adverse events for six months. The transfer of their reported data takes place every second month in parallel with the reevaluation of tumor therapy. Participants of the standard care group will report their occurred adverse events and duration only during their personal appointments. What the patient remembers and reports depends on each participant and is very individual. Based on these reported adverse events, physicians will delineate a CTCAE scoring. Physicians will additionally fill out an electronic case report form containing tumor stage and information about therapeutic substances and doses. Moreover, patients of both study arms will answer a questionnaire about life quality which is based on the European Organization for Research and Treatment of Cancer (EORTC) questionnaire at enrolment and once at the end of the study to investigate whether NEMO can improve the quality of life. |

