| Methods: Participants, interventions, and outcomes | | |
| Study setting | 9 | Study will be conducted at the University Hospital Ulm |
| Eligibility criteria | 10 | Inclusion Criteria:   - infusional combination therapy with at least two chemotherapy substances with or without further targeted therapies - combination of at least two immune-checkpoint inhibitors - able to read and understand German   Exclusion Criteria:  Participants who meet any of the following criteria will be excluded:   - severe neurological disorders   severe psychiatric disorders |
| Interventions | 11a | Not applicable. The study is to analyse the potential of new media for documentation. This can be considered as observational study. |
|  | 11b | Criteria for discontinuing are death, leaving Ulm or acquiring of exclusion criteria. |
|  | 11c | NEMO provides a user friendly interface for elderly individuals (clear design, big fonts, and auditory feedback) helping an easy fill in of questionnaires. |
|  | 11d | There are no interventions that are permitted or prohibited during the trial. |
| Outcomes | 12 | Primary Outcome:  Patient acceptance of a new medium of communication  Change of occurred adverse events  Secondary Outcome:  Maintenance of chemotherapy doses through better adverse event management  Change in the quality of life |
| Participant timeline | 13 | Both parts of the study are planned to last 6 months and build on each other (see Fig 1 and Table 4). |
| Sample size | 14 | Sample size was determined with the statistical software G*Power (v3.1.9.4) We assumed an effect size of 1, corresponding to a side effect variation of 1 on the Likert scale, a type I error rate = 0.05, and a power of 80%. Planning for a Mann-Whitney test comparing the difference between two groups led to a required sample size of 18 individuals per group (Fig 2). |
| Recruitment | 15 | The first part will be used to assed the right group of subjected that later on will allow random assignment in the second part of the study. |
| **Methods: Assignment of interventions (for controlled trials)** | | |
| Allocation: |  |  |
| Sequence generation | 16a | The physician's desktop application belonging to the app provides the pseudonym NEMO-Identifier for the participating test person. This is an isolated system that is independent of the smartphone app. |
| Allocation concealment mechanism | 16b | Method of random allocation of patient will be set in at the time of the beginning of the study. |

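### Patients on checkpoint inhibitors alone appear eligible, but the chemotherapy-dose outcome has no value for them; items 8, 10 and 12 need reconciling, and Part 2 should be stratified by regimen type

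*Protocol*

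**What the plan says.** Protocol item 10 (Eligibility criteria) has two therapy bullets with no connecting word between them: "infusional combination therapy with at least two chemotherapy substances with or without further targeted therapies" and "combination of at least two immune-checkpoint inhibitors". The second does not require chemotherapy.

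Item 12 (Outcomes) gives as a secondary outcome "Maintenance of chemotherapy doses through better adverse event management". It states no population, metric or denominator. Item 6a (Background and rationale) likewise gives as an aim of the second phase the effect of the app on side-effect management, "as well as the maintenance of the original chemotherapy dose".

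Item 8 (Trial design) is worded more broadly: Part 2 will "compare the impact of smartphone reported adverse events regarding applied therapy doses to those of patient with standard care". Physicians complete an "electronic case report form containing tumor stage and information about therapeutic substances and doses", which is not limited to chemotherapy. Item 8 also says that, according to the therapy scheme, "the NEMO questionnaire can be selected for chemotherapy (Table 1) or combined immunotherapy (Table 2), targeted therapy, and chemotherapy".

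On allocation, item 8 says that "36 participants will be randomly assigned a group of 18 persons (smartphone user and standard care"). Item 16b leaves the method of random allocation to be set when the study begins. No stratification factor is named anywhere. Item 20a plans a Wilcoxon-Mann-Whitney comparison of adverse-event severity between NEMO users and standard reporting, names no analysis of dose and mentions no regimen factor. Item 20b says that the statistical details are complete.

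**The concern.** A patient treated only with checkpoint inhibitors has no chemotherapy dose to maintain. If such patients can be randomised, the outcome in item 12 does not apply to everyone in Part 2, and the protocol does not say to whom it applies. Item 8 points to an outcome that would cover every patient. The result therefore depends on which item the analyst follows, and that choice would be made after the regimen mix is known.

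The second issue is smaller. The protocol itself separates the regimen types by giving them different side-effect questionnaires, so it expects their side effects to differ. With 18 patients per arm, a chance difference in regimen mix could add appreciable noise to both the severity comparison and any dose comparison. Nothing in the plan guards against this, although regimen type is known at enrolment.

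**Working it through.** **1. The plan's own figure.** Item 14 gives 18 per group for a Mann-Whitney test with effect size 1, type I error 0.05 and power 80%. Sidedness is not stated; two-sided is assumed here. With the normal-parent efficiency 3/π, the effective n is 18 × 0.955 = 17.19, the degrees of freedom are 2 × 17.19 − 2 = 32.4, and the noncentrality is 1 × √(17.19/2) = 2.93. Power is 81.2%. The same calculation at n = 17 gives 78.8%. So 18 per group reproduces. It was sized for side-effect variation, not for the dose outcome.

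**2. Are the item 10 bullets alternatives?**
- *Cumulative reading:* every patient would need at least two chemotherapy substances and at least two checkpoint inhibitors. Nobody would then be on chemotherapy alone, and the chemotherapy questionnaire (Table 1) would have little purpose.
- *Alternative reading:* some patients receive chemotherapy and others checkpoint inhibitors, and the questionnaire is chosen accordingly. This fits item 8 and the label of Table 2 as an immunotherapy questionnaire.

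The alternative reading is the natural one, but the text does not state it. The item 8 phrase on combined immunotherapy can also be read as immunotherapy given together with targeted therapy and chemotherapy.

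**3. Which patients have a dose outcome?**

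| Source | Dose compared | Checkpoint-inhibitor-only patient |
|---|---|---|
| Items 6a and 12 | chemotherapy | no value |
| Item 8, Part 2 aim | therapy | has a value |
| Item 8, case report form | substances and doses given | data recorded |

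The two definitions coincide only if no such patient is enrolled.

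**4. How many patients are affected?** The documents give no regimen mix. Let K be the number of checkpoint-inhibitor-only patients among the 36 (an assumption), so that 36 − K can be evaluated for a chemotherapy-dose outcome. With a fixed 18:18 split and no stratification, the number X of such patients in one arm is hypergeometric:

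P(X = x) = C(18, x) · C(18, K − x) / C(36, K), and the arms differ by |2x − K|.

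Example, K = 4: a difference of 4 needs x = 0 or x = 4, so P = 2 × 3,060 / 58,905 = 0.104.

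| K (assumed) | Evaluable, 36 − K | Mean per arm | P(difference ≥ 4) |
|---|---|---|---|
| 4 | 32 | 16 | 10% |
| 6 | 30 | 15 | 18% |
| 12 | 24 | 12 | 29% |
| 18 | 18 | 9 | 32% |

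For odd K the difference must itself be odd, so the figures are not directly comparable. At K = 9 the chance of a difference of 3 or more is 44%, and of 4 or more (in effect 5 or more) 12%.

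**The case against.** Four arguments on the other side carry weight.

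- **Allocation.** A reader might infer that the protocol prescribes unstratified allocation. It does not. Item 16b defers the method, so stratification is neither adopted nor excluded. What stands is that no factor is specified and that there is still time to specify one.
- **Bias.** A reader might also infer that unequal regimen mix would bias the trial. Under randomisation, chance imbalance adds variance; it does not bias the comparison in expectation or invalidate the rank test. The same could be said of other prognostic factors. Regimen type is singled out because the plan already treats the groups differently in data collection. The documents do not quantify its effect on severity or dose.
- **Outcome population.** It is tempting to say that item 12 applies the dose outcome to everyone and that checkpoint-inhibitor-only patients would count as maintained, diluting any difference between arms. Item 12 names no population, and nothing suggests such scoring. An outcome about chemotherapy doses could simply be meant for patients on chemotherapy, with the details left to a statistical analysis plan that is not shown. That would settle the metric. It would not remove the conflict between items 8 and 12, which lies in the protocol itself.
- **Eligibility.** With no connecting word in item 10, the cumulative reading cannot be excluded, and under it the problem disappears. Item 8 also allows the Part 2 recruitment criteria to be amended after Part 1. Either way, item 10 needs clarifying.

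**Conclusion.** The point holds as an inconsistency among items 8, 10 and 12, on the natural but not explicit reading that the item 10 bullets are alternatives. Patients with no chemotherapy dose can then be enrolled, one secondary outcome has no value for them, and the protocol implies two different denominators for it.

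The size depends on K, which the documents do not give. Over an assumed range of 4 to 18, between 32 and 18 of the 36 patients would contribute to a chemotherapy-dose outcome. Under a fixed, unstratified 18:18 split, a difference of 4 or more such patients has a probability of roughly 10% to 32% at even totals. These figures describe how often the arms would differ in composition. They do not measure a shift in any outcome.

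The sample size stands, and no stated power claim is broken, because the dose outcome was not powered. The case for stratifying is precision and protection against chance imbalance in a small trial. It is a cheap improvement, not the repair of a biased design.

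**What to change.** 1. **Item 10:** state whether the two therapy bullets are alternatives.
2. **Items 8 and 12 (and 6a):** use one dose outcome throughout. Either (a) restrict it to patients on a chemotherapy-containing regimen at randomisation and state that denominator, or (b) define it as the proportion of planned systemic therapy given, for all randomised patients. The case report form already records substances and doses given; for (b), make sure that the planned dose is recorded too. Classify regimen at randomisation, because item 8 allows the app setting to change when therapy changes.
3. **Items 16a and 16b:** when the allocation method is set, stratify Part 2 by regimen type (chemotherapy-containing, or checkpoint inhibitors only).
4. **Item 20a:** replace the single pooled Wilcoxon-Mann-Whitney comparison of the arms with one stratified by regimen type (van Elteren form).

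**Cost:** protocol wording and one stratification factor known at enrolment, with no extra patients. Option (a) leaves a smaller denominator for the dose outcome. With few checkpoint-inhibitor-only patients that stratum contributes little to the stratified test: at K = 4 it holds two per arm under balanced allocation.

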| Statistical methods | 20a | Wilcoxon-Mann-Whitney test will be used to assess known-groups validity, as well as to compare differences between NEMO users and patients with standard reporting procedure concerning the severity of occurred adverse events. NEMO uses a Likert scale to score each questionnaire item. To rate the overall effect of adverse event management, a summary score will be calculated from a weighted sum of questionnaire items by the maximum number of items. Spearman correlation will be used to evaluate convergent validity between each item and the summary score of the quality of life questionnaire or its symptom scales. The impact of the side effect management will be analyzed by comparing changes in an item's scoring between the reevaluation steps during tumor therapy. This comparison will be made using a Jonckheere-Terpstra test |
|  | 20b | All statistical details have been given. |
|  | 20c | We set up in NEMO reminders for the patients in order to minimize potential missing data points. |
| **Methods: Monitoring** | | |
| Data monitoring | 21a | Members of the protocol committee and biometry and statistical analysis will be in charge of monitoring the pseudonymised data. Statical approach for analysis is described above in section 20a-c. |
|  | 21b | For exclusion we refer to 10c. Interim data will be accessed by the committee described in 21a. Study leaders and coordinator will be in charge of deciding for study termination. |
| Harms | 22 | Not applicable to the trial. The aim of the trial is to assess new media communication for report and reduction of adverse events. |
| Auditing | 23 | Not applicable to the trial. |
| Ethics and dissemination | | |
| Research ethics approval | 24 | Consent was obtained in a written form by the ethics committee Ulm University, Ulm, Germany - Proposal no. 406/19. |
| Protocol amendments | 25 | All relevant involved parties will be informed of important protocol modifications. |
| Consent or assent | 26a | All patients will have to sign a written declaration of consent in order to participate to the study. All participants will be informed of procedure and endpoint. They will be also given the possibility to ask questions to coordinators before consenting to take part to the study. Also, possibility of withdrawing consent at any time is an option. |
|  | 26b | This point is not applicable to the study. No biological specimens will be taken. |

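### Items 10 and 11b, read together, can end participation because of a severe form of a side effect under study, so loss from the severity comparison can depend on the outcome

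*Protocol*

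**What the plan says.** - **Item 11b** (Interventions): "Criteria for discontinuing are death, leaving Ulm or acquiring of exclusion criteria". The verb shows that the rule operates during follow-up.
- **Item 10** (Eligibility criteria) gives two exclusion criteria: "severe neurological disorders" and the psychiatric counterpart. The lead-in is "Participants who meet any of the following criteria will be excluded". Neither criterion has a definition, a grade or a time point, and treatment-related events are not exempted.
- **Item 6a** (Background and rationale) says that the drug combinations "can cause side effects such as nausea, inflammation of the mucous membrane (mucositis), diarrhea (diarrhea) or polyneuropathy".
- **Item 12** (Outcomes) has as its second primary outcome "Change of occurred adverse events".
- **Item 20a** (Statistical methods) uses a Wilcoxon-Mann-Whitney test to "compare differences between NEMO users and patients with standard reporting procedure concerning the severity of occurred adverse events", and also compares item scores between re-evaluation steps.
- **Item 21b** (Data monitoring): "For exclusion we refer to 10c". The protocol has an item 10 but no item 10c.

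**The concern.** A rule that ends participation is harmless to a randomised comparison when its trigger has nothing to do with the outcome. Here the trigger may be an instance of the outcome. Polyneuropathy is one of the four side effects that the rationale gives as examples, and a severe case is, on a plain reading, a severe neurological disorder. A patient discontinued for it midway would have no later scores if collection stops at that point. No later analysis plan could recover scores that were never taken.

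The two arms are also not equally exposed to the rule. Allocation is open (item 17a). NEMO patients answer questions daily, while standard-care patients report at appointments what they happen to remember (item 8). An undefined criterion, applied by unblinded physicians with more information on one arm than on the other, can remove different numbers from each. The arms would then be compared on patients selected by severity.

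**Working it through.** **1. How the text leads to outcome-dependent loss**

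| Step | Source | Stated or inferred |
|---|---|---|
| Acquiring an exclusion criterion means discontinuation | 11b | stated |
| A severe neurological disorder is an exclusion criterion | 10 | stated |
| Polyneuropathy is a side effect of the therapies studied | 6a | stated |
| A severe treatment-related polyneuropathy meets the criterion | none | literal reading; nothing prevents it |
| Scoring stops, or the patient leaves the analysis | none | not stated either way |

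The first three steps make the loss possible. The last two are needed before it occurs.

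**2. The plan's own sample size (item 14)**

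Inputs: effect size d = 1, alpha 0.05, power 80%, Mann-Whitney test. Take the test as two-sided with a normal parent distribution, so the asymptotic relative efficiency is 3/π = 0.955. The power comes from a noncentral t with effective size n' = n × 3/π, df = 2n' − 2 and noncentrality d × √(n'/2).

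- n = 18: n' = 17.19, df = 32.4, noncentrality 2.93, power 0.812. The stated 18 per group is reproduced and is not disputed.
- 17, 16 and 15 per arm: power 0.788, 0.761 and 0.732.

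Eighteen is therefore the smallest size that reaches 80%, with no allowance for loss. These power figures describe loss for any reason and do not measure this point.

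**3. Illustration with no true effect**

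Assumptions, none from the protocol: a 0–4 score, rounded normal with mean 1.5 and SD 1, 18 per arm, two-sided Mann-Whitney test at 0.05. The worst m patients are dropped after ranking on the outcome itself. Results are from simulation, and ranges are across repeated runs.

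| Removed (one arm / other arm) | Shift in mean difference | Rejection rate |
|---|---|---|
| 1 / 0 | about -0.10 | about 6% |
| 2 / 0 | about -0.19 | 8–9% |
| 3 / 0 | about -0.28 | 12–13% |
| 2 / 1 | about -0.09 | 7–8% |
| 2 / 2 | 0 | about 7% |

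The last row matters for reading the others. Equal removal causes no shift but still gives about 7% rejection, so part of the excess comes from trimming extremes and not from a difference between arms.

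Item 20a also describes a summary score over many items, whereas removal would follow from one item. With 10 items, an assumed inter-item correlation of 0.3 and 2 patients removed from one arm on a single item, the shift is about -0.07 and rejection about 6%.

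**4. Illustration with a true effect of 1 SD**

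Assume control severity N(0,1), NEMO severity N(−1,1), and removal above a common cut-off c. The observed difference is 1 − φ(c)/Φ(c) + φ(c+1)/Φ(c+1).

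| Controls removed | NEMO removed | Observed difference | Simulated power |
|---|---|---|---|
| none | none | 1.00 | 0.81 |
| 5% | 0.4% | 1 − 0.109 + 0.012 = 0.90 | 0.76 |
| 10% | 1.1% | 1 − 0.195 + 0.030 = 0.835 | 0.72 |
| 20% | 3.3% | 1 − 0.350 + 0.076 = 0.73 | 0.62 |

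If NEMO works, the same rule removes mostly controls and hides part of the benefit. The bias can therefore run either way.

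**The case against.** The strongest reply is that two inferred steps carry the point. The neurological criterion sits beside a psychiatric one and a language requirement, so it may be meant to describe people unable to complete daily questionnaires. And a list of reasons for discontinuing does not say that earlier data are discarded or that scoring stops. App data are transferred every second month (item 8), so some severity data may exist before a patient stops. Analysis sets and the handling of discontinued patients commonly belong in a SAP, which is not shown here.

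Much of this stands. A reader might infer that patients with polyneuropathy are removed from the primary outcome, but the text does not say so. A reader might also call polyneuropathy a declared target of the app. It is only a named example: item 18a describes the app's questions as covering pain, food intake and well-being, and the questionnaire tables are not shown.

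The reply does not dispose of the point. The discontinuation rule is something the protocol states, not something left to a SAP. The narrower meaning of the criterion is as much an inference as the literal one, and the ambiguity itself lets physicians apply it differently. Item 20b declares the statistical details complete, item 20c offers only app reminders, and item 21b refers to an item that does not exist.

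**Conclusion.** The point holds as a defect of wording with a real route to bias. As written, items 10 and 11b allow a severe form of a side effect under study to end participation, and nothing secures the outcome data afterwards. Loss from the comparison in items 12 and 20a can then depend on severity and can differ by arm.

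Its size is unknown, because the protocol gives no rate of severe neuropathy or of discontinuation. The illustrations run from negligible to material. A type I error of 8 to 13% requires the 2 or 3 worst of 18 patients (11 to 17%) to be lost from one arm and none from the other, which is an extreme case. A reader might conclude that the rule produces a false benefit for NEMO or breaks the randomisation. The documents do not support that: it would need more removals in the NEMO arm, and loss of severe controls would bias the result against NEMO. The point is worth settling before the randomised part begins, since the correction is cheap and missing scores cannot be recovered later.

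**What to change.** 1. Reconcile items 6a, 10, 11b and 21b, including the reference to the missing item 10c.
2. State that the exclusion criteria apply at entry, so that acquiring one later does not by itself end outcome collection.
3. Where the patient remains able and consenting, continue the scheduled physician CTCAE scoring and the end-of-study QLQ-C30, whether or not the app is still used.
4. Analyse all patients in the arm to which they were randomised.

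This leaves tumour therapy untouched. It also leaves the other reasons for discontinuing as they are: relocation is a practical limit in a single-centre study and is not at issue here. The cost is a few sentences in the protocol and a few extra forms at visits that take place anyway.

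### Item 20a applies a test for independent groups (Jonckheere-Terpstra) to repeated scores of the same patients, and labels what is naturally a within-arm trend the impact of side effect management

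*Protocol*

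**What the plan says.** Item 20a (Statistical methods) states the purpose, "The impact of the side effect management will be analyzed by" "comparing changes in an item's scoring between the reevaluation steps during tumor therapy", and then the method: "This comparison will be made using a Jonckheere-Terpstra test". It also says what an item is: "NEMO uses a Likert scale to score each questionnaire item". The sentence names no arm, no pairing and no blocking by patient.

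Item 8 (Trial design) shows where the scores come from in part 2. In one arm "smartphone users will answer their respective NEMO questionnaires every day about occurred adverse events for six months", and the transfer of these data "takes place every second month in parallel with the reevaluation of tumor therapy". In the other arm, "Participants of the standard care group will report their occurred adverse events and duration only during their personal appointments".

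The same item 20a separately plans a Wilcoxon-Mann-Whitney test of adverse event severity between NEMO users and standard reporting. Item 14 sizes part 2 for a Mann-Whitney test, with 18 patients per group. Item 20b declares the statistical details complete.

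**The concern.** There are two separate problems.

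**The test does not fit the data.** Jonckheere-Terpstra is a trend test for independent samples in ordered groups. Here the ordered groups are points in time, and each patient appears in all of them. The variance used by the test ignores that, so the p-value does not have its nominal meaning.

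**The label does not fit the comparison.** NEMO items are completed by smartphone users only. On the natural reading the test therefore looks for a trend over time inside one arm. Such a trend can arise from the course of therapy, dose changes or the loss of the sickest patients. Calling it impact attributes it to the intervention without using the randomisation.

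At stake are power that 18 patients cannot spare (or, on other readings, too many false positives), and the risk that the ordinary course of toxicity is reported as an effect of the app. Change in adverse events is one of the primary outcomes in item 12.

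**Working it through.** **Inputs from the protocol.** 18 patients in the NEMO arm and nominal alpha 0.05 (items 8 and 14). Re-evaluation every second month over six months gives 6 / 2 = 3 steps, or 4 if baseline counts.

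**Assumptions, since the protocol gives no figures.** Five-level item (0 to 4), from a latent normal variable with SD 1 that is rounded; exchangeable within-patient correlation ρ of 0.5 or 0.7; two-sided 5% test.

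**The plan's own figure.** None is given for Jonckheere-Terpstra. The 18 per group belongs to the Mann-Whitney test and reproduces: effect size 1, two-sided 0.05, normal parent with relative efficiency 3/π gives n = 18 per group with power 0.81.

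**Reading 1: one raw score per patient per step.** With three steps the trend is essentially step 3 minus step 1. The test takes its variance as 2σ²/n; the true value is 2σ²(1 − ρ)/n. Hence the true level is about 2{1 − Φ(1.96/√(1 − ρ))}.
- ρ = 0.5: 1.96/0.707 = 2.77, giving about 0.6%.
- ρ = 0.7: 1.96/0.548 = 3.58, giving about 0.03%.

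A coarse item has a lower rank correlation than the latent ρ, so simulation (2,500 to 4,000 runs per cell) gives slightly higher values:

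| Steps | ρ | Type I error, J-T | Type I error, Page | Power for a fall of 0.2 per step, J-T v Page |
|---|---|---|---|---|
| 3 | 0.5 | 1.0 to 1.4% | about 5% | about 13% v 30% |
| 3 | 0.7 | 0.1 to 0.3% | about 5% | about 10% v 45% |
| 4 | 0.5 | 0.9 to 1.3% | about 5% | about 40% v 64% |
| 4 | 0.7 | 0.1 to 0.2% | about 5% | about 40% v 82% |

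At ρ = 0, Jonckheere-Terpstra holds its level (about 5%), which confirms that the repeated use of the same patients is the cause.

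**Reading 2: successive changes, as the wording literally suggests.**
- Three time points give two changes, y2 − y1 and y3 − y2. They share y2 with opposite sign, so their correlation is −0.5 whatever ρ is. The variance ratio is 1.5 and the level about 2{1 − Φ(1.96/√1.5)} = 2{1 − Φ(1.60)} = 11%. Simulated: 10 to 11%.
- Four time points give three changes. The trend is essentially the third minus the first, which share no observation, so the level is about 5% (simulated 4.4 to 5.2%).
- A steady fall of δ per step gives every change the same mean, −δ, so there is no trend among the changes. With a fall of 0.2 per step the rejection rate stays at its null value, about 10% or 5%.

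**Reading 3: all daily entries pooled by two-month period.** With an assumed patient-by-period share of 10% to 20% of the variance, the type I error is 11% to 19% with 10 entries per period and 42% to 55% with 60. If that share is zero, it is 0.5% to 1%.

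**Attribution.** Take a drift of 0.3 points per step with no NEMO effect, four steps and ρ = 0.5. Jonckheere-Terpstra rejects in about 82% of trials and Page's test in about 94%. Both correctly detect a real drift; neither says anything about NEMO. In a further simulation with an assumed decline of 0.8 SD in both arms, Jonckheere-Terpstra within the NEMO arm rejects in about 60% of trials, while a Mann-Whitney test on change between the arms rejects in 4.3% to 4.5%.

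**The case against.** **The trial is controlled.** A reader might infer that the trial has no control comparison and that its effect claim rests on Jonckheere-Terpstra alone. The protocol does not support that: 36 patients are randomised, item 20a plans a between-arm test on severity, and the sample size belongs to that type of test. The lack of a control holds for this one analysis only.

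**The restriction to NEMO users is inferred.** The sentence names no arm. Item 8 has physicians derive a CTCAE scoring, and item 18a stores app entries with a CTCAE score, so a common grade may exist in both arms. The within-arm reading follows from the word item and from who completes the items; it is the natural reading, not a stated one.

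**A conservative test does no harm.** A reader might take a wrong level to mean too many false positives. With raw scores the opposite is true, and the cost is lost power. But conservatism cannot be relied on: successive changes from three time points, or pooled daily entries, push the error above nominal.

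**The 82% might be read as a false positive rate.** It is not. The drift is real in that scenario, and a valid test finds it more often. The fault lies in the interpretation.

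**A statistical analysis plan could settle it.** Such a plan can add detail, but here the protocol names the unsuitable test and item 20b says nothing is outstanding.

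**Conclusion.** The point holds. The test named in 20a is unsuitable for repeated scores of the same patients. The distortion has no fixed direction: about 1% or less for raw scores at ρ of 0.5 or 0.7, about 10% for successive changes from three time points, about 5% but with almost no power for a steady fall from four, and possibly far above nominal for pooled daily entries. These sizes rest on assumed correlations, item distribution and variance shares. The principle does not.

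Separately, a within-arm trend, however tested, cannot carry the label impact. The documents do not support extending the criticism to the planned Mann-Whitney comparison or to the sample size; both stand.

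**What to change.** Replace the last two sentences of item 20a with text to this effect: *The impact of side effect management will be assessed between the randomised arms. For each patient one summary over the re-evaluations (for example the mean, or the change from enrolment) will be computed from a score available in both arms, such as the physician-derived CTCAE scoring, and the arms will be compared by the Wilcoxon-Mann-Whitney test. Any trend over the re-evaluation steps among NEMO users will be described with one score per patient per step and Page's trend test, and will not be interpreted as an effect of NEMO.*

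The protocol should confirm that the chosen score is recorded in both arms and state which steps count, including whether baseline does. A mixed model with arm and visit is an option but is not needed.

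The cost is a wording change, a little analysis work and a weaker label for the within-arm result. The sample size does not change.
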